### Study population

The study cohort will include individuals aged 35 years or over with T2DM (with ≥1 diagnostic code as in (online supplementary table S1) between 1 April 2007 and 31 March 2017. Patients with an ever record of type 1 diabetes (see online supplementary table S2) will be excluded unless they have records of non-insulin anti-diabetic therapies. We chose the study period after 2006 as the quality of CPRD data has improved substantially to adhere with the then introduced important changes to the national incentive scheme The Quality and Outcomes Framework (QOF), an incentivisation programme for all GP surgeries in the UK.^20 21^ QOF exception reporting process allows general practices to exclude patients from indicators or a clinical domain based on discretionary exception codes. However, evidence on the use of exception codes has shown that they are being used appropriately by practices and overall exception rates for diabetes patients are low.^22^

10.1136/bmjopen-2017-020926.supp1Supplementary data

For this cohort construction, we will consider implementing previously validated algorithms designed to identify diabetes cases by avoiding potential misclassification in routinely collected data such as CPRD.^23 24^ Eligible patients will be followed up until censored at the earliest instance of any of the following event dates: patient transferred out of the practice (any cause), last collection date for the practice, the study end on 31 March 2017 or death. The main demographic and clinical characteristics of the defined diabetes cohorts (such as age, gender, geographic region within England, patient-level and general practice-level social deprivation, body mass index (BMI) and baseline glycated haemoglobin (HbA_1c_)) will be identified. Based on our previous studies, the expected sample size in a year will include 11 000 patients with T2DM registered with English general practices linked to the HES Admitted Patient Care data set, HES Outpatient and HES A&E data sets. A random 80% of the identified diabetes cohort (training dataset) will be used to develop the severity tool, with the remaining 20% of the cohort used as a validation data set, as described below.

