### Statistical analyses

#### Diabetes severity algorithm

Using annual data bins and grouping diabetes patients in the training data set (include random 80% of the total diabetes cohort) from 1 April to 31 March between 2007 and 2017, the developed diabetes algorithm will grade the severity of T2DM using predefined (sub)domains. Our study period (after 2006) was selected to ensure very high data quality in primary care, while the addition of secondary care data will make our analyses even more robust, in terms of accurately classifying T2DM severity levels.

We will consider two approaches to derive numerical or categorical diabetes severity scores or levels. First, we will use a binary classification (severity indicator: present/absent) within each subdomain and calculate an aggregate score. The second approach, through hierarchical stratification of end organ microvascular and macrovascular complications, will involve increasing weighting within each subdomain, as severity increases where scores of 1, 2 or three on each subdomain will be assigned based on clinical input in terms of severity. Then, regression models, using death (primary outcome) and future hospitalisation (secondary outcome) as dependent variable, will be fitted from which the weights of its estimates will be used to calculate the weights for severity subdomains. The highest possible severity score will be known when the final list of included domains and subdomains is decided. Hierarchical diagrams of the clinical severity of identified diabetes-related complications domains (figure 1), cerebrovascular domains (figure 2) and cardiovascular (figures 3 and 4, online supplementary figures S1 and S2) domains are presented.

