#### Longitudinal trends of diabetes severity

In patients newly diagnosed with T2DM, during the study period, we will assess the temporal trends of severity scores over time by calculating the time needed to progress along the quintiles of the severity scale starting from the date or year of diagnosis and identify the predictors to this progression across quintiles.

While the inclusion of some domains such as carotid artery stenting, the use of ACEIs or lipid-regulating drugs, kidney transplantation and laser therapy are clinically relevant and represent markers of greater level of disease severity, they also improve the prognosis (lessen the grade of severity), that is, raising a risk of ‘feedback’. While we will further assess their role, we may have to not include these domains in the modelling at the analysis stage. All statistical analyses will be conducted using Stata Statistical Software for Windows: Release 15 (StataCorp LP, College Station, Texas, USA).

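### Progression counted only as movement across score quintiles gives unequal credit for equal worsening, cannot register it in top-quintile starters, and can produce false predictors unless the analysis conditions on the starting score

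*Protocol article*

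**What the plan says.** In the protocol article, under Longitudinal trends of diabetes severity, the population is defined as "In patients newly diagnosed with T2DM, during the study period". The measure is "calculating the time needed to progress along the quintiles of the severity scale starting from the date or year of diagnosis", and the second step is to "identify the predictors to this progression across quintiles". No other measure of progression is given.

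The section Diabetes severity algorithm describes the score. It proposes "two approaches to derive numerical or categorical diabetes severity scores or levels", computed in annual bins. The first approach is to "use a binary classification (severity indicator: present/absent) within each subdomain and calculate an aggregate score", which gives a discrete count with ties. The range is open: "The highest possible severity score will be known when the final list of included domains and subdomains is decided".

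The article does not say which population or period sets the quintile cut-offs, how patients already in the top quintile are handled, or whether the predictor analysis takes account of the starting score.

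**The concern.** Quintiles equalise numbers of patients, not widths on the score. The event therefore depends on two things: how much a patient worsens, and how close the patient stood to the next cut-off at diagnosis. Only the first is of interest. In the top quintile the event cannot occur at all.

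This matters most for the predictor step. Any characteristic associated with the score at diagnosis is also associated with the distance to the next cut-off and with the chance of starting at the ceiling. The validation section itself plans to examine how scores vary with characteristics such as age, ethnicity and deprivation, so such associations are expected. An analysis that ignores the starting score could report them as drivers of worsening.

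The Introduction lists trajectories over time and the identification of complex patients among the intended uses. A progression measure with a ceiling serves both poorly.

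**Working it through.** The protocol gives no event rate, effect size or power for this analysis, so there is no figure to reproduce. Every distribution below is an assumption.

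**1. Which gains count.** Take a count score that is Poisson with mean 2. Its cumulative probabilities at 0, 1, 2 and 3 are 0.135, 0.406, 0.677 and 0.857, so the 20th, 40th, 60th and 80th percentiles are 1, 1, 2 and 3. Two cut-offs coincide and only four groups exist: 0–1, 2, 3, and 4 or more. A one-point gain counts from 1, 2 or 3, but not from 0 or from 4. For a continuous gamma score (shape 1.5), the quintile widths between the 1st and 99th percentiles are 0.45, 0.43, 0.54, 0.85 and 3.35.

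**2. Same worsening, different chance of an event.** Let every patient gain a Poisson number of points at 0.4 per year for 5 years (mean 0.4 × 5 = 2), and let the starting score be negative binomial with mean 3 and size 2. The starting probabilities for 0 to 5 are 0.160, 0.192, 0.173, 0.138, 0.104 and 0.075. Cut-offs from scores at diagnosis are 1, 2, 3 and 5.

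- P(gain ≥ 1) = 1 − e⁻² = 0.865; P(gain ≥ 2) = 1 − 3e⁻² = 0.594.
- Lowest quintile: a start at 0 needs 2 points and a start at 1 needs 1 point, so (0.160 × 0.594 + 0.192 × 0.865) / 0.352 = 0.74.
- Second and third quintiles (scores 2 and 3): 0.865 each.
- Fourth quintile: a start at 4 needs 2 points and a start at 5 needs 1 point, so (0.104 × 0.594 + 0.075 × 0.865) / 0.178 = 0.71.
- Top quintile (6 or more): 0.
- Overall 0.656 progress, so 1 − 0.656/0.865 = 24% of patients who gained at least one point are not counted.

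With a starting mean of 5 (size 3) this share is 33%. With cut-offs taken from a cohort of longer duration it is about 40%.

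**3. False predictors.** Simulation with 2,200 patients, 5 annual steps and 40 replicates. A binary covariate multiplies the mean score at diagnosis by 1.5 or 2 and has no effect on worsening (0.3 points per year in both groups). The outcome is time to the first move above the starting quintile, in a Cox model.

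| Analysis | Result (ratio 1.5; 2, or range) | Replicates significant |
|---|---|---|
| All patients, cut-offs from scores at diagnosis, count score | HR 0.87; 0.78 | 68%; 100% |
| Same, continuous score | HR 0.74; 0.60 | 100%; 100% |
| All patients, cut-offs from pooled patient-years, count score | HR 1.00; 0.92 | 12%; 33% |
| Same, continuous score | HR 0.84; 0.73 | 95%; 100% |
| Top-quintile starters excluded | HR 0.95–1.11 | 3–45% |
| Excluded, and stratified by starting quintile | HR 1.02–1.09 | 0–28% |
| Excluded, and conditioned on starting score | HR 0.99–1.01 | 0–10% |
| Regression of 5-year change in score | difference −0.016 to +0.011 points | 3–12% |

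A covariate unrelated to the starting score showed no bias (HR 0.99–1.01).

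**4. Second model.** With the step 2 inputs, n = 100,000 and age correlated 0.4 with the starting score but not with worsening, the odds ratio of progression per SD of age was 0.76–0.78 with cut-offs from scores at diagnosis. It was about 1.16–1.25 with cut-offs from scores shifted upwards by Poisson(2.8), which mimics longer duration. With top-quintile starters excluded and the starting score as a factor, it was within about 0.02 of 1 in every scenario.

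**5. Size of the ceiling.** The share starting in the top quintile was 20% for a continuous score cut at diagnosis. It was 4–6% (count) or 8–12% (continuous) with pooled cut-offs, and 5–6% with longer-duration cut-offs.

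**The case against.** A reader might infer that the plan will produce false predictors. The article does not support that. It names no model, covariates or risk set, and an analysis plan would ordinarily supply them. If top-quintile starters are excluded and the starting score is conditioned on, the artefact all but disappears. This stands, and the point is worded accordingly.

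A reader might also infer that the false association reverses direction with the choice of reference. That happened only with the assumed shift in step 4; pooled patient-years in step 3 gave hazard ratios of 0.73 to 1.00. The direction cannot be predicted from the document.

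The ceiling may touch few patients if cut-offs come from the whole cohort and newly diagnosed patients start low. That is plausible but not assured. Table 1 includes hypertension, previous myocardial infarction, depression and any-cause admissions, all of which can precede a diabetes diagnosis.

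Quintiles of the scale could mean equal fifths of its range. The unequal widths would then go, but distance to the next boundary would still matter and the top band would still have no exit.

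Nor is worsening in the sickest patients lost from the whole study: scores are computed yearly, described, and related to outcomes elsewhere. The blind spot lies in this progression analysis.

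Conditioning removes the predictor bias only. It does not change which gains count or give top-quintile starters an event to reach.

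**Conclusion.** The concern holds in a limited form. The unequal credit and the ceiling follow from the chosen outcome when quintiles are cut on the score distribution; they are not details left for later. False predictors are a conditional risk: they need a covariate related to the score at diagnosis and an analysis that does not condition on that score. Stratifying by starting quintile reduces the bias but does not reliably remove it.

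The simulated figures rest on assumed score distributions, equal worsening and no deaths, and step 3 used only 40 replicates. They show that the effect can range from negligible to large; they do not estimate its size in this study. The analysis is not the main aim, which is to build and validate the score, but the remedy is cheap enough to justify the change.

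**What to change.** Under Longitudinal trends of diabetes severity:

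- Make change in the annual score the main progression measure, for example with a mixed model containing time since diagnosis and predictor-by-time terms. If a time-to-event summary is wanted, use time to a fixed gain in points, adjusted for the starting score.
- Keep quintile movement as a descriptive transition table by starting quintile. State the reference population for the cut-offs and show top-quintile starters separately.
- If only a categorical score results, condition the predictor analysis on the starting level and exclude top-level starters from the risk set.

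The cost is new analysis wording and a different model on scores already planned; no further data are needed. Points per year are less simple to explain than quintile steps, which is the reason to retain the descriptive table.

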**Methods and analysis:**

Primary care data from the Clinical Practice Research Datalink, linked hospitalisation and mortality records between April 2007 and March 2017 for patients with T2DM in England will be used to develop a clinical algorithm to grade T2DM severity. The EHR-based algorithm will incorporate main risk factors (severity domains) for adverse outcomes to stratify T2DM cohorts by baseline and longitudinal severity scores. Provisionally, T2DM severity domains, identified through a systematic review and expert opinion, are: diabetes duration, glycated haemoglobin, microvascular complications, comorbidities and coprescribed treatments. Severity scores will be developed by two approaches: (1) calculating a count score of severity domains; (2) through hierarchical stratification of complications. Regression models estimates will be used to calculate domains weights. Survival analyses for the association between weighted severity scores and future outcomes—cardiovascular events, hospitalisation (diabetes-related, cardiovascular) and mortality (diabetes-related, cardiovascular, all-cause mortality)—will be performed as statistical validation. The proposed EHR-based approach will quantify the T2DM severity for primary care performance management and inform the methodology for measuring severity of other primary care-managed chronic conditions. We anticipate that the developed algorithm will be a practical tool for practitioners, aid clinical management decision-making, inform stratified medicine, support future clinical trials and contribute to more effective service planning and policy-making.

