### Severity domains

A systematic literature search for studies that developed algorithms or models to assess and quantify the severity of diabetes was conducted to identify the domains and subdomains for T2DM severity (to be published separately). Also, expert clinical opinion from members of the research team was used to supplement the search process and identify possible omissions. Clinical members in the team include pharmacists ([name], [name]), GPs (CS, CM, [name], [name] and NQ), a consultant diabetologist ([name]) and a consultant cardiologist (MM), who used their expertise to create a list of relevant clinical domains for T2DM severity. The final domains to be included in the severity model will be decided during the analysis stage. Currently, the identified clinical domains that are relevant to the degree of progression of T2DM include: patient factors (diabetes duration (the period between T2DM diagnosis and the severity score estimation) and BMI), monitoring laboratory tests (HbA_1c_ categories (threshold of 7% [53 mmol/mol]), and blood glucose levels), type of anti-diabetic therapy, other prescribed medications (such as lipid-regulating medications and ACE inhibitors (ACEIs)), comorbidities (including diabetes-related complications, depression), hospitalisation and surgical interventions. Comorbidities will be identified using appropriate code lists and contribute to the severity score according to each score computing method. The identified domains and subdomains are described in table 1. Domains will also be reviewed by a panel of ‘experts by experience’ (people with lived experience of T2DM) to provide patient validation of the severity scoring tool.

**Table 1 T1:** The main (sub)domains identified to quantify the severity of type 2 diabetes

	Severity domain	Severity subdomain
1.	Risk factors*	Duration of type 2 diabetes^40^ Body mass index (BMI) Hypertension Hyperlipidaemia Personal/Family history of cardiovascular disease Blood glucose levels Glycated haemoglobin (HbA_1c_)^35^ Fasting blood glucose (FBG) and random blood glucose (RBG)
2.	Type/pattern of anti-diabetic treatment, insulin use and other therapies	Anti-diabetic therapy ever;^40^ Therapies with cardiovascular benefits versus other; Changes in drug treatments;^43^ or the number of prescribed treatments^42^ Insulin use: prescription ever or within 1 year of diagnosis; Insulin initiation:^15^ time to initiation Other therapies: ACE inhibitors (ACEI) and lipid-regulating therapies

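### Diabetes duration is both an input to the severity score and the time axis of the progression analysis, so some apparent progression is only elapsed time

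*Protocol article*

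**What the plan says.** The abstract lists the provisional severity domains as "diabetes duration, glycated haemoglobin, microvascular complications, comorbidities and coprescribed treatments". Table 1 has "Duration of type 2 diabetes" as the first subdomain under risk factors. The Severity domains section defines the item as "diabetes duration (the period between T2DM diagnosis and the severity score estimation". The list is not final: "The final domains to be included in the severity model will be decided during the analysis stage".

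The Diabetes severity algorithm section gives two ways of scoring. In the first, "we will use a binary classification (severity indicator: present/absent) within each subdomain and calculate an aggregate score". In the second, "scores of 1, 2 or three on each subdomain will be assigned based on clinical input in terms of severity". Regressions on death and on hospitalisation then supply the weights. No weight, duration cut-off or quintile boundary is given.

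The section on longitudinal trends takes patients newly diagnosed during the study period and describes "calculating the time needed to progress along the quintiles of the severity scale starting from the date or year of diagnosis", followed by identifying predictors of that movement. The same section says that some domains may have to be left out because they both mark severity and improve prognosis. Its examples are treatments and procedures; duration is not among them.

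**The concern.** The duration item in the score and the clock of the progression analysis are the same quantity. Every newly diagnosed patient starts at duration zero, and the item can only grow. If it carries a positive weight, a patient whose HbA1c, complications, comorbidities and treatment have not changed still gains score and may cross a quintile boundary. The analysis would report that as progression.

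The predictor analysis inherits the problem. Under an upward shift common to all patients, crossing a boundary depends partly on how close to it the patient started, and this can weaken the apparent effect of real predictors.

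The longitudinal use is not incidental. The abstract and the Discussion present grading over time as a purpose of the tool. The section on clinical implications suggests that longitudinal patterns could make the tool more relevant than HbA1c and a more reliable basis for practice remuneration. A score that worsens in stable patients would undermine that use.

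**Working it through.** The article states no figure for this analysis, so there is nothing to reproduce. The check has a logical part and an illustration on assumed inputs.

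**Logic.** Let t be time since diagnosis. The score is S(t) = w·f(t) + R(t), where f is the coding of duration and R collects all other subdomains. By the definition in the Severity domains section, the argument of f is t, which is also the axis of the progression analysis. f does not decrease under any plausible coding (present/absent, 1/2/3 or linear). With w > 0 and R constant, S rises or stays level and never falls. Without duration, S(t) = R(t), and a patient with constant R never moves.

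**Illustration, all patients followed for 10 years.** Assumed: normal score with SD 0.6, quintile cut-points fixed at diagnosis, linear duration weight of 0.02, 0.03 or 0.05 log-HR per year, R constant. Ten years is the length of the study window.
- Cut-points: 0.6 × (−0.842, −0.253, 0.253, 0.842) = −0.505, −0.152, 0.152, 0.505.
- Shift after 10 years: 0.2, 0.3 or 0.5.
- Share moving up = sum over the four cut-points c of P(c − shift < S < c), with each interval kept within its own quintile.
- Shift 0.2: 0.080 + 0.121 + 0.132 + 0.106 = 0.439.
- Shift 0.3: 0.110 + 0.174 + 0.197 + 0.166 = 0.648.
- Shift 0.5: 0.153 + 0.200 + 0.200 + 0.200 = 0.753.

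The ceiling is 0.80, because the top fifth cannot move up.

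**Illustration with realistic follow-up.** Assumed: diagnosis uniform over the 10 years, death 0.03 and transfer out 0.05 per year (0.08 combined).
- Probability of being followed beyond t: G(t) = (1 − t/10)·exp(−0.08t).
- Mean follow-up: 1/0.08 − (1 − e^(−0.8))/(0.08² × 10) = 12.5 − 8.60 = 3.90 years. The median is 3.4 years.
- Averaging the share moving up over this follow-up distribution:

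| Weight per year | All followed 10 years | Staggered entry and losses |
|---|---|---|
| 0.02 | 44% | 17% |
| 0.03 | 65% | 26% |
| 0.05 | 75% | 39% |

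**Present/absent coding.** Assume one point is added at an assumed 5-year cut-off. G(5) = 0.5 × e^(−0.4) = 0.335, so about 34% are followed long enough to receive it. For count scores with assumed baseline means of 1.5 to 4, 62 to 81% of patients who receive the point move up. That gives 0.335 × 0.62 to 0.335 × 0.81, or about 21 to 27% overall.

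**Different score structures.** Assume cut-points from 11 000 prevalent patients with durations of 0 to 20 years, 9, 30 or 45 other binary subdomains held constant, and 9.9 years of follow-up. Among patients below the top quintile at diagnosis, 53 to 87% move up with a binary duration item (5-year cut-off), 81 to 86% with 1/2/3 scoring (cut-offs at 3 and 7 years), and 27 to 87% with linear weights of 0.05 to 0.2 points per year. With duration left out the figure is 0% throughout. These shares have a different denominator from the table and assume near-complete follow-up.

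**The case against.** The domain list is provisional, so duration might yet be dropped. It is also a deliberate part of the severity concept: the section on prior studies faults an existing index for lacking it. The Introduction's aims are to develop the score and to validate it against outcomes, and the overlap harms neither. All of this stands, and it lowers the severity of the point. It does not remove it: duration is a current domain, it is not among those flagged for possible removal, and nothing takes it out of the progression analysis.

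The size is uncertain. Large percentages need long follow-up or generous weights, and a present/absent item adds only one step. That is accepted; the lower figures with realistic follow-up are the fairer guide.

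A reader might infer three stronger claims that the article does not support:
- **That total scores must climb through the quintiles.** Only the duration component must rise. HbA1c and BMI are averaged within time windows, and look-back periods of 3 to 5 years are planned, so other inputs can improve or drop out. Duration-specific quintiles would also remove the drift, though the article does not propose them.
- **That times to progression will be averaged over patients seen to progress, and so be too short.** The longitudinal section names no estimator. Censoring rules are given under Study population, and survival methods under the validation section. The choice may properly sit in the full analysis plan.
- **That predictors would be driven towards determinants of follow-up length.** This does not follow from a common shift when follow-up is censored.

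**Conclusion.** The point holds as a definitional overlap: as written, elapsed time since diagnosis is counted as worsening severity in an analysis meant to measure worsening severity. The direction is certain whenever duration has a positive weight. The size is not, because weights, coding and cut-points are not given. With log-HR weights of 0.02 to 0.05 per year and a score SD of 0.6, about 17 to 39% of clinically unchanged patients move up a quintile under the assumed entry, death and transfer pattern, and 44 to 75% with 10 years of follow-up for all. This should be fixed. It is not critical to the study, because it leaves score development and outcome validation untouched.

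**What to change.** For the longitudinal analysis and its predictors, make a score recomputed without the duration subdomain the main version, and show the full score alongside so that readers can see how much of the movement is elapsed time. Take the quintile cut-points once from the training set and hold them fixed, separately for each version of the score. Do not test duration as a predictor of progression. Keep the full score, with duration, for the validation analyses.

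The cost is a few sentences in the plan and one extra version of the score, with no new data. The drawback is that the main longitudinal score then differs from the validated one; showing both and stating the reason deals with that.
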